## Background

Eclampsia is a serious pregnancy complication that occurs when a pregnant woman - or new mother - experiences seizures associated with hypertension. These seizures pose a major risk to the life and the health of mothers and unborn babies. Signs or symptoms of severe preeclampsia are not always present or easy to recognise before a woman develops eclampsia. This is why it can be difficult to tell which women are likely to develop eclampsia before the first seizure occurs. If we can identify the features that are most common and unique to eclampsia, these could be used to develop a tool to help identify the women displaying signs or symptoms that occur prior to the onset of eclamptic seizures. This would mean that treatment to prevent seizures could be targeted to the right women and quickly administered before they become extremely unwell with this life-threatening complication.

The development of a tool to predict eclampsia in high-resource settings (such as Australia) has been largely hampered by the extremely low prevalence of this complication1. This makes it challenging for researchers in this setting to conduct impactful studies and obtain reliable and detailed information about the characteristic features of eclampsia. However, rates of eclampsia, like many other complications, are far greater in low to middle income countries (LMICs; including South Africa, Pakistan and the Solomon Islands), with an estimated 16-69 cases of eclampsia per 10,000 livebirths2,3. Thus, research conducted in LMIC settings allow for the prospective recruitment of a relatively large cohort of women with eclampsia. They are a useful target population to prospectively characterise the signs and symptoms preceding the disease. *Such characterisation may yield a unique clinical signature for eclampsia and the development of a predictive algorithm.*

## Aims

**Aim 1:** To characterize the clinical signs and symptoms that occur prior to the onset of eclampsia in a prospectively collected cohort.

**Aim 2:** Compare these characteristics to women with preeclampsia and healthy normal pregnancies to identify which features represent a unique clinical signature for eclampsia to form a simple predictive algorithm.

## Study design

This is a multicentre prospective observational study in which women will be consecutively recruited, with four centres currently recruiting:

- Tygerberg Hospital, Cape Town South Africa
- Fatima Memorial Hospital, Lahore, Pakistan
- Jinnah Hospital, Lahore, Pakistan

Clinical signs and symptoms experienced by the women prior to enrolment in this study will be centrally recorded via the online database Research Electronic Data Capture (REDCap) and used to identify the presence or absence of a unique clinical signature able to predict imminent eclampsia.

Chief investigators at each site will be responsible for training and familiarising recruiting and study staff with the use of the REDCap and online data collection via the supplied iPad.

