**Inclusion criteria**

*Eclampsia:*

- Diagnosed as new onset generalized tonic colonic seizures or coma in pregnant women or women who have recently given birth.
- Singleton pregnancies.
- All gestational ages, including post-partum eclampsia
- Enrolment to the study must occur within 7 days of an eclamptic episode
- Women must be coherent and able to provide informed consent prior to enrolment

*Preeclampsia:*

- Diagnosed as new onset of hypertension (>140 mmHg systolic or > 90 mmHg diastolic) after the 20th week of gestation and the coexistence of one or more of the following new onset conditions:
  - Proteinuria
  - Other maternal organ evolvement:
    - renal insufficiency (creatinine >90 umol/L)
    - liver involvement (elevated transaminases and/or severe right upper quadrant or epigastric pain)
    - neurological complications
    - haematological complications (thrombocytopenia, DIC, haemolysis)
  - Uteroplacental dysfunction
    - Fetal growth restriction
- All gestations >20 weeks
- Singleton pregnancies
- Have not experience an eclamptic episode

*Normotensive controls:*

- Healthy normotensive pregnant woman recruited from women seeking maternity services during the same or similar time period
- Matched by closest gestation and parity.

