## Outcome measures

The primary outcome is the presence or absence of a clinical signature of imminent eclampsia, unique both from women with preeclampsia and healthy normotensive pregnant women. To determine this, we have designed a standardised questionnaire collecting the following information:

| Maternal characteristics | Obstetric/booking information | Signs/symptoms | Eclampsia | Outcome |
| --- | --- | --- | --- | --- |
| First name | Gestation at booking | Highest systolic BP | Date of onset | Delivery date |
| Last name | Date at booking | Highest diastolic BP | Location of onset | Gestation at delivery |
| Maternal age | Estimated due date | Highest proteinuria | Prior magnesium sulphate | Indication for delivery |
| Address | How was due date estimated | Lowest platelet count |  | Mode of delivery |
| Race | Height | Highest AST |  | Live born |
| Marital status | Weight | Lowest haemoglobin |  | Sex |
|  | Antenatal care | Edema |  | Birthweight |
|  | Gravidity/parity | Tendon reflexes |  | Apgar at 5 minutes |
|  | Previous viable pregnancy outcome | Headaches, severity and onset |  | Neonatal outcome |
|  | Systolic BP at booking | Visual disturbances/type and onset |  | Number of days in hospital (maternal) |
|  | Diastolic BP at booking | Epigastric pain |  | Adverse maternal outcome |
|  | Proteinuria at booking | Tightness in chest |  |  |
|  | Antihypertensive medication | Shortness of breath |  |  |
|  | Tobacco/alcohol/drug use | Focal neurological deficit |  |  |
|  | Diabetes | Nausea/vomiting |  |  |
|  | Chronic hypertension | Confusion |  |  |
|  | Cardiovascular disease | Twitching/jerking of extremities |  |  |
|  | Anaemia | Mind state |  |  |
|  | HIV status | Concentration |  |  |
|  | Respiratory disease | Speech |  |  |
|  | Inflammatory bowel disease | Hearing |  |  |
|  | Autoimmune disease | Changes in moods |  |  |
|  | Malaria | Dizziness |  |  |
|  | Renal disease | Weakness or paralysis |  |  |
|  | Neurological disease | Jitters/nervousness |  |  |
|  | Medication use |  |  |  |

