## Statistical analysis

Data will be collected and analysed in clinically relevant categories with I2 or Mann-Whitney U tests used to detect difference between groups. We will compare data from women with eclampsia to those with i) preeclampsia and ii) normotensive pregnancies, to determine the unique signs and symptoms that precede eclampsia. Odds ratios will be used to determine strength of association for clinical characteristics significantly associated with eclampsia. We will also attempt to create a predictive score for eclampsia.

1. Knight M. Eclampsia in the United Kingdom 2005. *BJOG: An International Journal of Obstetrics & Gynaecology.* 2007;114(9):1072-1078.

3. Frias AE, Jr., Belfort MA. Post Magpie: how should we be managing severe preeclampsia? *Current opinion in obstetrics & gynecology.* 2003;15(6):489-495.

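### The stated window for signs ends at enrolment, which follows the seizure in every eclampsia case, so consequences of the seizure can be counted as signs that precede it

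*Protocol*

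**What the plan says.** Three parts of the protocol bear on when a sign must occur.

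- **Recording rule.** Study design gives the only explicit time limit: "Clinical signs and symptoms experienced by the women prior to enrolment in this study will be centrally recorded". The same sentence says the recorded signs are "used to identify the presence or absence of a unique clinical signature able to predict imminent eclampsia".
- **Entry of cases.** Under Inclusion criteria, an eclampsia case is defined by a seizure or coma. "Enrolment to the study must occur within 7 days of an eclamptic episode", and "Women must be coherent and able to provide informed consent prior to enrolment".
- **Purpose.** Aim 1 is "To characterize the clinical signs and symptoms that occur prior to the onset of eclampsia". The Statistical analysis section compares the groups "to determine the unique signs and symptoms that precede eclampsia".

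The Outcome measures table lists the candidate items. An onset is listed for headaches and for visual disturbances only. Confusion, mind state, concentration, speech, weakness or paralysis, and focal neurological deficit appear without one. Extremes such as "Highest systolic BP", lowest platelet count, highest AST and lowest haemoglobin have no time limit. For the eclampsia itself the table lists a date and a place of onset, but no clock time.

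**The concern.** The recording rule and the aim end at different moments. The aim needs a window that closes at the first seizure; the rule closes it at enrolment. In eclampsia cases the interval between the two always exists and may last days.

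This bears on the primary outcome, a clinical signature that separates eclampsia from both preeclampsia and normotensive pregnancy. A sign produced by the seizure itself cannot occur in either comparator group. If it is recorded as preceding, it can look unique to eclampsia because of the recording rule alone, and it has no value for predicting the seizure that caused it. Enrolling more women would not remove the error, only make the false association more certain to reach significance.

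This is not a matter of recall. A woman who remembered perfectly everything up to enrolment would still report post-seizure signs under this rule.

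**Working it through.** The protocol states no sample size, sign prevalence or error rate, so there is no figure of its own to reproduce. The check is first textual and then an illustration.

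**Step 1: order of events in a case.** The case is defined by the seizure or coma, and she must be coherent to consent. So enrolment follows the seizure in every case. The permitted gap is up to 7 days, counted from an episode that is not stated to be the first. With repeated seizures the gap from the first could be longer.

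**Step 2: the two windows side by side.**

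| Source (Protocol) | Window for signs ends at |
| --- | --- |
| Study design | enrolment |
| Aims, Aim 1 | onset of eclampsia |
| Statistical analysis | eclampsia (signs must precede it) |

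The first window contains the other two plus the post-seizure interval.

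**Step 3: can the listed data separate before from after?** For headaches and visual disturbances, partly: an onset on a day after the seizure date can be removed. With only a date for the seizure, ordering within the same day is not assured. For the other neurological items and for the extremes, the table lists no time, so they cannot be separated from the listed data. An analysis plan could not restore an ordering that was never collected.

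**Step 4: illustration of size. All rates here are assumptions.** Let p be the true pre-seizure prevalence of a sign, equal in cases and comparators (true odds ratio 1). Let q be the share of cases without the sign who first show it between seizure and enrolment and have it recorded as preceding.

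Recorded prevalence in cases = p + (1 − p)q.

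Recorded odds ratio = [p + (1 − p)q] / [p(1 − q)].

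For p = 10%, q = 20%: 0.10 + 0.90 × 0.20 = 0.28, and 0.28 / (0.10 × 0.80) = 3.5.

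The last column is the probability of a two-sided 5% finding with an assumed 100 women per group.

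| p | q | Recorded prevalence in cases | Recorded odds ratio | Chance of a false finding |
| --- | --- | --- | --- | --- |
| 5% | 10% | 14.5% | 3.2 | 62% |
| 5% | 20% | 24% | 6.0 | 97% |
| 10% | 10% | 19% | 2.1 | 44% |
| 10% | 20% | 28% | 3.5 | 91% |
| 30% | 10% | 37% | 1.4 | 18% |
| 30% | 20% | 44% | 1.8 | 54% |

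The distortion is largest for signs that are rare before the seizure. With the window closed at the first seizure, q = 0 and the odds ratio is p / p = 1.

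**The case against.** The strongest reply is that the intent is plain. Background, Aim 1 and the Statistical analysis section all speak of signs before the disease. The Study design sentence covers three groups, two of which have no seizure, so its reference to enrolment may be loose general wording. The interview form is not shown, and its questions may already ask about the time before the fit.

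Much of this stands, and it limits what can be claimed. A reader might infer that post-seizure signs *are* being counted; the documents show only that they *can* be. Nor does the coherence requirement show that incoherence is recorded as a sign, since it is a condition of consent. The onset fields for headaches and visual disturbances give partial protection for those two items.

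A reader might also infer that effects of treatment and delivery contaminate cases alone. The documents do not support that. Women with preeclampsia have no enrolment deadline and are not barred from enrolling after treatment or delivery. In post-partum eclampsia, delivery comes before the seizure. Only direct consequences of the seizure are confined to cases by definition.

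Finally, the illustration uses invented rates and assumes that every acquired sign is recorded as preceding. It shows how the error would work, not that it has occurred.

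What the reply does not remove is the contradiction. The only explicit recording limit names a moment later than the aim allows, and most listed items carry no timing that could correct it.

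**Conclusion.** The point holds as a contradiction within the protocol that reaches the primary outcome. The recording rule in Study design admits post-seizure signs and values into a signature meant to precede the seizure, and the listed items do not allow them to be taken out again, apart from part of the headache and visual data. It should be corrected before the signature is analysed.

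Confidence is high for the conflict of wording. The amount of contamination is unknown: it depends on a form that is not shown and on how often each sign first appears after the seizure. At an assumed 10% prevalence with 10% or 20% acquired, a null sign would show an odds ratio of 2.1 or 3.5; over the whole range tabulated, 1.4 to 6.0. None of these is an estimate for this study.

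It might also be inferred that the 7-day enrolment limit is at fault. It is not: it governs eligibility, not the sign window, and once the window closes at the first seizure the length of the gap no longer determines which signs count. Restricting the limit to the first episode could exclude women with recurrent seizures to no purpose.

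**What to change.** - **Study design:** state that for eclampsia cases the window for signs and measurements ends at the first seizure or coma.
- **Outcome measures and the REDCap form:** for each sign, record whether it was present before the first seizure, with the options *yes*, *no*, *only after* and *cannot say*. Record the date and time of the first seizure and of each highest or lowest value.
- **Statistical analysis:** let only pre-seizure data enter the signature, and hold later values separately.
- **Comparators:** state a comparable index time for the preeclampsia and normotensive groups. Otherwise closing the window for cases alone creates a new imbalance.
- **Inclusion criteria:** leave the 7-day rule as it is.

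The cost is protocol wording, one response field per sign, a few time fields and local retranslation of the form. No extra participants are needed. Some signs in cases will become *cannot say* and be lost to the signature analysis. The protocol says centres are already recruiting, so women already enrolled will need their items re-derived from the chart where possible. That takes staff time and will not always succeed.

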## Recruitment

Women presenting with eclampsia, preeclampsia or healthy pregnancies will be eligible to participate, with recruitment aiming to enrol *all women with eclampsia or preeclampsia at each site*.

**Inclusion criteria**

*Eclampsia:*

- Diagnosed as new onset generalized tonic colonic seizures or coma in pregnant women or women who have recently given birth.
- Singleton pregnancies.
- All gestational ages, including post-partum eclampsia
- Enrolment to the study must occur within 7 days of an eclamptic episode
- Women must be coherent and able to provide informed consent prior to enrolment

*Preeclampsia:*

- Diagnosed as new onset of hypertension (>140 mmHg systolic or > 90 mmHg diastolic) after the 20th week of gestation and the coexistence of one or more of the following new onset conditions:
  - Proteinuria
  - Other maternal organ evolvement:
    - renal insufficiency (creatinine >90 umol/L)
    - liver involvement (elevated transaminases and/or severe right upper quadrant or epigastric pain)
    - neurological complications
    - haematological complications (thrombocytopenia, DIC, haemolysis)
  - Uteroplacental dysfunction
    - Fetal growth restriction
- All gestations >20 weeks
- Singleton pregnancies
- Have not experience an eclamptic episode

*Normotensive controls:*

- Healthy normotensive pregnant woman recruited from women seeking maternity services during the same or similar time period
- Matched by closest gestation and parity.

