**Exclusion criteria**

- Women with multiple pregnancies.
- Women with seizures attributed to a diagnosis other than eclampsia such as; central nervous system infections, a history of seizures or epilepsy, medications and/or illicit drug use.
- Women unable to provide informed consent

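### Recruitment aims at every woman with eclampsia, but only those coherent and consenting within 7 days can contribute data; the rest are not counted, so severe and early fatal cases are under-represented

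*Protocol*

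**What the plan says.** Under Study design, the Protocol calls itself a "multicentre prospective observational study in which women will be consecutively recruited". Under Recruitment, the goal is to enrol "all women with eclampsia or preeclampsia at each site". Under Inclusion criteria, eclampsia is defined as "new onset generalized tonic colonic seizures or coma in pregnant women or women who have recently given birth", so coma alone qualifies.

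The same list of eclampsia criteria adds two conditions: "Enrolment to the study must occur within 7 days of an eclamptic episode" and "Women must be coherent and able to provide informed consent prior to enrolment". Neither appears in the lists for preeclampsia or normotensive controls. Exclusion criteria then remove, from all three groups, "Women unable to provide informed consent". Ethical approval asks for written consent from every patient before enrolment.

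Data collection and management makes everything conditional on that consent: enrolment, the structured interview, the review of medical charts, and follow-up to postpartum discharge. The Protocol describes no proxy, deferred or chart-only route, and no record of eligible cases that were not enrolled.

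**The concern.** The primary outcome is whether a clinical signature of imminent eclampsia exists that separates these women from those with preeclampsia and from healthy pregnancies. The signs of interest occur before the seizure, but a woman enters the case group only if her course after the seizure lets her consent in time. If pre-seizure signs are related to that later course, the prevalence of a sign among enrolled cases differs from its prevalence among all cases, and the odds ratios shift with it. The questionnaire includes confusion, state of mind, speech and focal neurological deficit, for which such a link is plausible, although the Protocol does not establish one.

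Two consequences do not depend on that link. The recorded adverse maternal outcomes cannot include deaths before consent. And without a count of missed cases, a reader cannot judge how far the enrolled women represent the population named under Recruitment. No later analysis can recover women who were neither recorded nor counted.

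**Working it through.** **Setting the provisions side by side.** The Protocol gives no figure for the share of cases lost, so there is nothing to reproduce. The first step is to follow each type of case through the rules.

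| Woman with eclampsia | Meets the definition | Can be enrolled | Data held |
| --- | --- | --- | --- |
| Seizure or coma, coherent and consents by day 7 | Yes | Yes | Interview, chart, outcome to discharge |
| Enrolled, then deteriorates or dies | Yes | Yes | As above, outcome recorded |
| Dies before regaining capacity | Yes | No | None, not counted |
| Regains capacity after day 7 | Yes | No | None, not counted |
| Never regains capacity | Yes | No | None, not counted |

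The last three rows follow from the wording alone.

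**What this could do to an odds ratio.** Every input here is assumed. Let *f* be the share of all cases not enrolled, *p* the prevalence of a sign in enrolled cases, *q* its prevalence in missed cases and *c* its prevalence in preeclampsia. Then

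- all-case prevalence: P = (1 − f)·p + f·q
- all-case odds ratio: [P/(1 − P)] / [c/(1 − c)]

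Take p = 0.10 and c = 0.05. The odds ratio from enrolled women is (0.10/0.90)/(0.05/0.95) = 0.1111/0.0526 = 2.11. Setting q to 0 and to 1 gives bounds that need no assumption about the missed women's signs:

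- f = 0.05, q = 0: P = 0.95 × 0.10 = 0.095; odds ratio (0.095/0.905)/0.0526 = 1.99
- f = 0.05, q = 1: P = 0.095 + 0.05 = 0.145; odds ratio (0.145/0.855)/0.0526 = 3.22
- f = 0.20, q = 0: P = 0.80 × 0.10 = 0.08; odds ratio (0.08/0.92)/0.0526 = 1.65
- f = 0.20, q = 1: P = 0.08 + 0.20 = 0.28; odds ratio (0.28/0.72)/0.0526 = 7.39

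The same formula with intermediate values of q:

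| Share missed (f) | q = 0 (none) | q = 0.10 (same as enrolled) | q = 0.40 | q = 1 (all) |
| --- | --- | --- | --- | --- |
| 5% | 1.99 | 2.11 | 2.47 | 3.22 |
| 10% | 1.88 | 2.11 | 2.84 | 4.46 |
| 20% | 1.65 | 2.11 | 3.62 | 7.39 |

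**A common sign.** With p = 0.60 and c = 0.40, the enrolled odds ratio is (0.60/0.40)/(0.40/0.60) = 2.25. If 20% of cases are missed, the all-case value is 1.91 when q = 0.40 (P = 0.56), 2.25 when q = 0.60, and 2.67 when q = 0.80 (P = 0.64).

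The enrolled odds ratio can therefore be too low, too high or correct, depending on *q*, which the study cannot observe, and on *f*, which it could count at little cost. These are ranges for the point estimate and ignore sampling error. No power figure is given, because it would need invented group sizes.

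**The case against.** Much can be said for the rule. The Recruitment wording is an aim, and it is normally read subject to the eligibility criteria, which state the restriction openly. Coma at diagnosis and coherence at enrolment concern different times, so one woman can satisfy both. Many items, such as headache onset, visual disturbance, mood and concentration, can only come from an interview, and a short window plausibly limits recall error. Personal written consent is also the stated ethics rule for everyone. The coherence and consent conditions are therefore defensible, and the point is not that they should be dropped.

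Three stronger readings are tempting, and the documents do not support them.

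- A reader might infer that the signature comes from milder cases only. It does not: there is no severity ceiling, and a woman who was comatose and recovers within 7 days is eligible.
- A reader might infer that women who die are never recorded. That holds only for deaths before consent; enrolled women are followed to discharge with outcomes recorded.
- A reader might infer that odds ratios are pulled towards 1. That requires missed cases to show the sign more often than enrolled ones, which the Protocol nowhere says. If they have the same prevalence there is no bias, and if lower, for instance because onset was abrupt, the odds ratio is too high.

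Nor is the loss wholly one-sided. The consent exclusion covers all groups, and a woman with preeclampsia too ill to consent is lost too. Only the explicit coherence condition and the 7-day limit are specific to cases, although after a seizure or coma the consent rule is likely to fall mainly on them.

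These objections limit the claim about bias. They do not answer the missing count, or the gap between the population named and the population that can be enrolled.

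**Conclusion.** The point stands as one about selection and applicability. As written, entry to the case group depends on the post-seizure course, and women who die before consent or regain capacity after day 7 contribute neither data nor a count. The case group therefore under-represents the most severe and pre-consent fatal cases, and adverse maternal outcome omits deaths before consent. This follows from the text and needs no assumption.

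Whether the odds ratios are biased, which way and by how much cannot be determined from the Protocol. The numerical ranges rest on assumed prevalences and an assumed missed share of 5% to 20%; they show how far an estimate could move, not how far it does. The change should be made because the uncertainty can be measured only if missed cases are counted while recruitment is under way.

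**What to change.** 1. **Log.** Have each site keep an identifier-free log of every eclampsia case not enrolled, one line per case, by reason: died, not coherent within 7 days, refused, other. Report enrolled and non-enrolled counts by site.
2. **Bound.** Report the main odds ratios for enrolled cases together with a bound that assigns each sign to none, then all, of the non-enrolled cases. With *x* of *N* enrolled cases showing the sign and *M* missed, the case prevalence runs from x/(N + M) to (x + M)/(N + M).
3. **Population.** Reword Recruitment, and limit the conclusion, so that the case population is women with eclampsia who survived and regained capacity to consent within 7 days.

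The cost is a short amendment and one log line per missed case, with no extra visits or procedures. The drawback is that the bounds may be wide: in the illustration above, 1.65 to 7.39 when 20% of cases are missed. A wide bound would itself show how little is known about the women not enrolled.

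Enrolling women who regain capacity after day 7 for chart-recorded items only is an optional addition, subject to ethics approval. It would leave their interview items missing and would not recover deaths, so it does not replace the log.

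### Normotensive controls are matched on gestation and parity, but the named tests treat the groups as independent, which can shrink odds ratios and make the significance screen conservative

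*Protocol*

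**What the plan says.** In the Protocol, Inclusion criteria, the normotensive controls carry a selection rule that the other groups do not: "Matched by closest gestation and parity". The group they are matched to, the ratio and the tolerance are not given.

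The preeclampsia group has only an eligibility range, "All gestations >20 weeks". Eclampsia enters at "All gestational ages, including post-partum eclampsia". Under Recruitment the aim is to enrol "all women with eclampsia or preeclampsia at each site", so neither of these groups is selected on gestation or parity.

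The Statistical analysis section then treats both comparators alike: "Data will be collected and analysed in clinically relevant categories with I2 or Mann-Whitney U tests used to detect difference between groups". The symbol printed as I2 is evidently chi-squared. The two contrasts are set out as "We will compare data from women with eclampsia to those with i) preeclampsia and ii) normotensive pregnancies". Effect size follows only for features that pass the test: "Odds ratios will be used to determine strength of association for clinical characteristics significantly associated with eclampsia". No paired test, conditional model, stratification or adjustment is mentioned, and nothing says that the odds ratios will be unadjusted.

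**The concern.** Matching makes the women in a set alike on gestation and parity, and therefore alike on any sign that depends on them. Chi-squared and Mann-Whitney tests assume that no such likeness exists. Their standard error is then too large for the matched comparison, and an odds ratio from the pooled two-by-two table is closer to 1 than the within-set odds ratio.

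The test also acts as a gate, because only significant characteristics go on to an odds ratio. A feature lost to a conservative test may drop out of the signature, and the primary outcome is a signature that is distinct from both comparators. One contrast has gestation and parity removed by design and the other does not, yet the two are read together.

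**Working it through.** **No figure to reproduce.** The Protocol states no sample size, alpha, power, effect size or matching ratio. Everything below rests on assumed inputs.

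**Normotensive contrast: inputs (all assumed).** 1:1 perfect matching, 150 pairs, two-sided alpha 0.05, and a sign with 30% frequency among controls in an average set. The log-odds of the sign vary across sets with standard deviation SD because of gestation and parity.

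**Model.** logit P(sign) = logit(0.3) + u + log(OR) × case, with u ~ N(0, SD²) shared within a pair. Let p1 and p0 be the frequencies in cases and controls averaged over u.

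- Unmatched OR = p1(1 − p0) / [p0(1 − p1)].
- Under no association, the unpaired variance term is V = 2p0(1 − p0). The correct paired term is V − 2C, where C is the within-pair covariance. True type I error = 2[1 − Φ(1.96 × √(V/(V − 2C)))].

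**Worked case, SD 1, true OR 3.** Averaging gives p1 = 0.5518 and p0 = 0.3310. Unmatched OR = (0.5518 × 0.6690) / (0.3310 × 0.4482) = 0.3692 / 0.1484 = 2.49. For the test, V = 2 × 0.3310 × 0.6690 = 0.4429 and C = 0.0359, so V − 2C = 0.3711. Then √(0.4429/0.3711) = 1.0925, 1.96 × 1.0925 = 2.141, and the type I error is 3.2%.

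| SD | Odds ratio of sign, set +1 SD vs −1 SD (e^(2·SD)) | p1 | p0 | True OR 3 appears as: integrated (simulated) | Type I error: integrated (simulated) |
|---|---|---|---|---|---|
| 0 | 1 | 0.5625 | 0.3000 | 3.00 | 5.0% |
| 0.5 | 2.7 | 0.5591 | 0.3096 | 2.83 (2.85) | 4.4% (4.6%) |
| 1 | 7.4 | 0.5518 | 0.3310 | 2.49 (2.5) | 3.2% (3.3%) |
| 1.5 | 20 | 0.5443 | 0.3539 | 2.18 (2.2) | 2.1% (2.0%) |
| 2 | 55 | 0.5380 | 0.3740 | 1.95 (2.0) | 1.2% (1.2%) |

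The simulated values use 150 pairs; the small differences are finite-sample effects and simulation noise. A true OR of 1 stays at 1 for every SD.

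**Power by simulation, chi-squared versus McNemar.** For a true OR of 2: about 80% versus 81% at SD 0.5, and 58% versus 70% at SD 1.5. For a true OR of 3 at SD 1.5: about 95% versus 97.5%.

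**Preeclampsia contrast: inputs (all assumed).** Take a sign with log-odds −1 in parous women (frequency 0.2689), and an odds ratio of 2.5 between nulliparity and the sign (frequency 0.4791 in nulliparous women). Nulliparity is 70% in eclampsia and 40% in preeclampsia, with no true association.

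- Eclampsia: 0.7 × 0.4791 + 0.3 × 0.2689 = 0.416.
- Preeclampsia: 0.4 × 0.4791 + 0.6 × 0.2689 = 0.353.
- Unadjusted OR = (0.416 × 0.647) / (0.353 × 0.584) = 1.31.

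With 60% versus 50% and an odds ratio of 1.5, the result is 1.04. With equal parity it is 1.00.

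The direction can reverse. Suppose a sign is present in 30% before and 50% after a gestation cut-off, with 50% of cases and 75% of comparators past it. The frequencies are 0.5 × 0.5 + 0.5 × 0.3 = 0.40 and 0.75 × 0.5 + 0.25 × 0.3 = 0.45. The unadjusted OR is (0.40 × 0.55) / (0.45 × 0.60) = 0.81.

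**The case against.** The strongest reply has four parts.

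1. **The size depends on SD.** At SD 1.5, gestation and parity alone must move a sign's odds about 20-fold between sets one SD either side of average. At SD 0.5 the loss is negligible. This stands: the effect may be small for many signs.
2. **The matching is loose.** The Protocol says closest, not exact, and gives no ratio. Cases may be postpartum while controls are pregnant. A paired analysis is therefore not compulsory. This stands too, and the remedy allows an ordinary model with the matching factors included.
3. **The target is debatable.** Part of the shift from 3 to 2.2 is the gap between a conditional and a marginal odds ratio rather than error. With a predictive aim, an unadjusted odds ratio among consecutively enrolled women with eclampsia or preeclampsia is a legitimate description of discrimination. This stands for preeclampsia. It helps less for the normotensive contrast, where matching has fixed the controls' gestation and parity mix, and it does not remove the test's conservatism.
4. **Adjustment may be in an analysis plan.** This is fair for the preeclampsia contrast, where the Protocol is merely silent. It is weaker for the normotensive contrast, where the Protocol names specific tests that do not fit its own sampling.

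A reader might infer that both sets of odds ratios are biased. The documents do not support that. The normotensive odds ratios move only if a sign depends on gestation or parity and is truly associated with eclampsia. The preeclampsia odds ratios are confounded only if those factors are imbalanced and also linked to the sign, and the Protocol gives no figures for either.

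**Conclusion.** The mismatch between matched selection and independent-group tests is on the face of the Protocol and holds for the normotensive contrast. Its consequence is conditional: attenuation towards 1 and a conservative screen, negligible at SD 0.5 and material from about SD 1 upwards, under assumed perfect 1:1 matching with 150 pairs and 30% baseline frequency. It does not raise the false-positive rate.

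For preeclampsia, the supportable statement is that the odds ratios may be confounded by gestation or parity in an unknown direction, and that they are not on the same footing as the normotensive ones.

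This is a should-fix point. Treating it as a fault that invalidates the analysis would go too far, since much of it can be repaired at analysis if gestation and parity are available.

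**What to change.** In the Statistical analysis section:

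- Analyse eclampsia versus normotensive by logistic regression that includes gestation and parity. If matched sets are kept, use conditional logistic regression instead, with McNemar or Wilcoxon signed-rank for simple 1:1 displays. Base the significance screen on the same analysis.
- For eclampsia versus preeclampsia, report odds ratios adjusted for gestation and parity beside the unadjusted ones, so that the two contrasts can be compared.

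In the Inclusion criteria, state which group the normotensive controls are matched to. If sets are to be used, add a set identifier to each site's database now: sites are already recruiting, the data list under Outcome measures shows no such field, and pairing that is not recorded may not be recoverable.

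The cost is a revised paragraph, a little more analysis work and one data field if sets are kept. Parity and due date are already on the data list. An index date at which gestation is taken in the comparators is not listed and would need to be defined.
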